## Abstract

**Background:**

Addiction constitutes a major public health problem, and despite treatment, relapse rates remain very high. Preliminary findings suggest that Eye Movement Desensitization and Reprocessing (EMDR), an evidence-based treatment for PTSD, may also reduce craving and relapse rates when applied in substance abuse. This study aims to determine the feasibility, efficacy and effectiveness of EMDR when added to treatment as usual (TAU) for addiction in alcohol dependent outpatients, compared to TAU only.

**Methods/Design:**

A single blinded study in which 100 adult patients with a primary DSM-IV-TR diagnosis of alcohol dependence or abuse receiving treatment in one of six Dutch outpatient addiction care facility sites, will be enrolled. After baseline assessment participants will be allocated to one of two treatment conditions (allocation ratio of 1:1) using a stratified (per site, per care pathway), blocked randomization procedure. The intervention consists of EMDR (seven weekly 90 minute sessions) + TAU or TAU only. Assessments are scheduled pre-treatment (t0), post-treatment (t0 + eight weeks), and one and six months post treatment. The effects of both treatment arms are compared on indices of (a) drinking behavior, (b) mediators, moderators and predictors of treatment outcome, (c) quality of life and d) safety, acceptability and feasibility of treatment.

Repeated measures ANOVA’s will be conducted using an intention-to-treat and per-protocol approach. Multiple imputation will be used to deal with missing values when possible.

**Discussion:**

This study adapts and extends the standard EMDR treatment for traumatized patients for use with patients with alcohol use disorders without psychological trauma.

**Trial registration:**

ClinicalTrial.gov: NCT01828866

## Background

In 2013 in the Netherlands, 46% of all treatment seeking patients with an addiction problem (more than 65.000) sought help for alcohol-related problems [1]. However, despite treatment, addictions such as alcohol dependence are characterized by high relapse rates [2]. For 1-year outcomes across alcohol, nicotine, and illicit drug abuse, more than 85% of patients relapse within 1 year of treatment.

Many factors are implicated in the genesis, escalation and maintenance of addiction. Here some known predictors of alcohol use are discussed before we introduce a relatively new approach to target some of these mechanisms in order to reduce drinking behavior. A multi-factorial approach is adopted to gain insight into possible mechanisms of change regarding this approach.

### Mediators, moderators and predictors of alcohol use and relapse

Addiction can be conceptualized as a cyclic process of anticipation, intoxication, and withdrawal [3]. The anticipation stage is considered a key element of relapse and often takes the form of intense craving. Craving refers to a compelling or intense urge, desire or intention to ingest a drug [4]. High baseline levels of alcohol craving may define a subtype of alcohol dependence that is less responsive to treatment and predict the chance of relapse after discharge [5]. In addition to craving itself it may be interesting to look at related concepts, such as desire thinking and rumination, which seem to augment craving.

Desire thinking refers to the elaboration of cognitions and imagery in working memory which may escalate craving intensity [6]. It correlates with escalating levels of drinking status [7]. Desire thinking is regarded as a specific type of perseverative thinking, such as rumination or worry [6]. Interestingly, rumination predicts long term outcomes of addiction treatment in alcohol-dependent patients [8]. Rumination increases craving in alcohol-dependent drinkers but not in problem and social drinkers [9]. So both desire thinking and rumination increase or intensify craving. Since rumination results in increased negative affect [10], it is no surprise that both low positive and high negative affect are associated with relapse in addiction [11]. So when levels of desire thinking and rumination are reduced, craving and negative affect may also be reduced, which would result in lower relapse rates.

In addition to these subjective processes, automatic implicit processes such as attentional biases have also been implicated in the maintenance of addiction [12,13]. Since alcohol attentional biases have a reciprocal excitatory relationship with craving, reductions in attentional bias should predict reductions in craving and drinking behavior. Whereas craving, desire thinking, rumination and negative affect are typically measured by subjective participant report, the strength of implicit processes may be measured more objectively in paradigms using changes in reaction times as primary outcome.

Other known predictors of alcohol treatment outcome which will be assessed in this study are baseline alcohol consumption, dependence severity, employment, gender, psychopathology rating, treatment history, motivation, socioeconomic status/income and self-efficacy [14]. Increased self-efficacy during treatment predicts a positive treatment outcome while an excess of self-efficacy can be inconsistent with the actual ability of a patient to resist use and may result in drop-out.

In sum, there is a large body of research on predictors of alcohol treatment outcome. These factors should be taken into account when aiming to reduce relapse rates since they can help identify at an early stage which interventions may have the highest clinical effectiveness over time. In addition, they provide important targets for direct intervention.

In this study we focus on an approach which targets episodic drug memories to reduce craving, alcohol consumption and relapse rates: Eye Movement Desensitization and Reprocessing (EMDR) [15].

### Research on EMDR in addiction

EMDR is a structured treatment for posttraumatic stress disorder (PTSD) [16]. The core of the procedure entails the identification and reactivation of specific memory representations in working memory while the patient follows the therapist’s horizontal hand movements with her or his eyes. Since this taxes working memory and working memory is limited in capacity, the eye movements compete for attention with the reactivated memory [17]. Every 30 seconds, the patient reports spontaneous associations, which form the focus of attention during a new set of eye movements. Over time the memory representation gets less vivid and emotionally charged (‘desensitisized’) while a new, more adaptive self-perspective tends to arise [18]. The EMDR procedure can also be used to desensitize dysfunctional positive memory representations [19] or that of anticipated events [20].

Research has clearly demonstrated EMDR’s effect in the treatment of PTSD [21]. Some have suggested that, on the basis of an emerging body of research, EMDR may be regarded as a general model for psychotherapy for a wider range of conditions, such as addiction [22]. However, research on the efficacy and effectiveness of EMDR on addiction is still limited, consisting mostly of anecdotal reports or case studies of substance-related [23-31] as well as behavioral addictions [32-37]. Although most of these reports and case studies found positive results, some found mixed [30] or negative results [24,25]. The interpretation of results is further complicated by the fact that different approaches were used [36,38,39].

To date, one RCT has been published [15]. Detoxified, in-patient alcohol dependent patients received TAU plus two one-hour sessions of EMDR targeting memory representations of intense craving or relapse. Controls received TAU only. Decreased craving at 1-month follow-up, as well as a lower relapse rate at 1- and 6-month follow-up were found in the experimental group. However, the sample size was small (n = 34), attrition was high, assessment depended fully on self-report and treatment was applied by the researcher. This raises questions about the actual efficacy and effectiveness of EMDR. In addition, although no adverse effects were reported, this study showed that relapse or study drop-out rates may still be substantial and should be taken into account when determining the feasibility of the treatment.

In sum, although limited data and methodological issues prohibit firm conclusions, further research on the efficacy of EMDR in addiction is warranted.

### Objectives

#### Primary objective – effects of treatment on drinking behavior

This study examines the efficacy and effectiveness of EMDR + TAU versus TAU only on drinking behaviour in a sample of alcohol dependent participants.

We operationalize drinking behavior as: a) changes in number of heavy drinking days (days on which ≥ 5 standard drinks of alcohol are consumed); b) time to first alcohol drink (only relevant if abstinence was reached before the previous assessment); c) changes in total drinks consumed in the past 30 days; and d) changes in average drinks per occasion in the past 30 days (total drinks divided by drinking days). Participant-reported information is backed-up with changes in relevant biomarker data (derived from blood samples at all time-points): carbohydrate-deficient transferrin (CDT) combined with serum γ-glutamyltransferase (GGT). An overview of the measurements at different time points is given in Table 1.

**Table 1 Tab1:** **Measurements of primary, secondary and tertiary objectives: drinking behavior, mediators, moderators and predictors and quality of life**

	Outcome	Measurement	Baseline screening	T0	T1	T2	T3
		-interview (i)		Pretreatment	Posttreatment	1 month FU	6 months FU
		-self-report (s)					
		-reaction time (r)					
		-bloodsample (b)					
1	Recent and lifetime use, indications for psychiatric or medical evaluation, addiction treatment history and current abuse or dependence (DSM-IV)	MATE (part 1–4) (i)	X				
2	Comorbid psychiatry (DSM-IV)	MINI-plus (i)	X				
3	Motivation to change	RCQ-D (s)		X			
4	Harmful alc. use	AUDIT (30 d) (s)		X	X	X	X
5	Self-efficacy	SELD (s)		X	X	X	X
6	Health outcome	EQ-5D (s)		X	X	X	X
7	Quality of life	CRA-HS (s)		X	X	X	X
8	Alcohol craving	PACS (s)		X	X	X	X
9	Desire thinking	DTQ (s)		X	X	X	X
10	Pos. and neg. affect	PANAS-SF (s)		X	X	X	X
11	Rumination	PTQ (s)		X	X	X	X
12	Drinking behavior	TLFB (30 d) (i)		X	X	X	X
13	Alcohol attentional bias	Alcohol Stroop (r)		X	X	X	X
14	Alcohol implicit assoc.	Valence IAT (r)		X	X	X	X
15	Biomarkers chron. alc. use	GGT + CDT (b)		X	X	X	X

*AUDIT* Alcohol Use Disorders Identification Test, *CDT* carbohydrate-deficient transferrin, *CRA-HS* Community Reinforcement Approach Happiness Scale, *DSM-IV* Diagnostic and Statistical Manual – 4th ed., *DTQ* Desire Thinking Questionnaire, *EQ-5D™* EuroQol - 5 dimensions, *GGT* serum γ-glutamyltransferase, *IAT* Implicit Association Task, *M.I.N.I.-plus* M.I.N.I. International Neuropsychiatric Interview-Plus, *PACS* Penn Alcohol Craving Scale, *PANAS-SF* Positive And Negative Affect Schedule – Short Form, *PTQ* Perseverative Thinking Questionnaire, *RCQ-D* Readiness to Change Questionnaire - Dutch version, *SELD* Self-Efficacy List for Drug users, *TLFB* Timeline Followback.

The primary outcome variable is changes in number of heavy drinking days since escalating numbers of heavy drinking days may best reflect a (temporarily) loss of control of drinking behavior, while the other behavioral outcomes could also reflect (to some degree) social or controlled drinking behavior.

#### Secondary objectives – mediators, moderators and predictors of treatment outcome

To explore mechanisms of change, variables that are potential predictors, mediators or moderators of treatment outcome will be examined (see Table 1). We distinguish:Dependent variables:Psychological (participant report): desire thinking, craving, rumination, negative affect and coping self-efficacy,Psychological (reaction times): alcohol attentional bias and implicit associations towards alcohol cues.Covariates:Measured at baseline: demographic characteristics, time-in-treatment, comorbid psychopathology, alcohol consumption, alcohol dependence severity, other substance use and readiness to change;Measured between baseline and follow-up: completer status, time-in-treatment, treatment intensity, the use of psychopharmaca, anticraving (naltrexone and acamprosate) or alcohol abstinence enforcing medication (disulfuram).

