### Interventions

#### Treatment as usual (TAU)

All participants already receive TAU at the moment they are enrolled and will continue to receive TAU for as long as indicated by their regular therapists but at least until T1. TAU may differ in intensity or additional components delivered (e.g. family treatment) between participants. In IrisZorg, most out-patients of care pathway ‘youth’ and ‘addiction’ receive (Adolescent) Community Reinforcement Approach ((A)CRA) treatment, consisting of several interventions, based on behavioral therapy principles [48]. Elements may include: functional analysis, training communication and/or problem-solving skills, sobriety sampling, social networking, learning to refuse substances, increasing alternative reinforcing activities, relapse management and medication monitoring. Treatment is individual but may also be partly groupwise. Patients receive TAU on a weekly basis by a health care worker.

Alternatively, some patients in care pathway ‘young’ may receive an intensive family treatment for youngsters up to 20 years old (and their families), who still live at home (or intend to go back to live at home again) and where multiple life domains may be affected (e.g. family, school, mental health, criminal behavior etc.): Multidimensional Family Therapy (MDFT [49]). Patients of care pathway ‘addition, care and housing’ receive Function Assertive Community Treatment (FACT [50]), a multidisciplinary, outreaching approach aimed at stabilization, treatment and recovery.

TAU is supervised by a clinical psychologist or psychiatrist. If necessary, treatment may be supplemented with medical care (such as, but not limited to medication), individual psychological care or relationship or family therapy. Incidentally or periodically, additional in-patient treatment may be necessary. CRA and MDFT typically lasts 6 months (in some cases CRA may be limited to 3 or extended to 9 months) while FACT may endure much longer.

‘Time-in-treatment’ before intervention and during the course of the study as well as main components and treatment intensity of TAU will be registered. The use of psychofarmaca, craving reducing (acamprosate, naltrexone) or abstinence enforcing medication (disulfuram) will be monitored.

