#### Fidelity checks

EMDR therapists receive one full and two half-days of training in the EMDR treatment protocol. All EMDR therapists will be supervised by an EMDR consultant to guide optimal application of the treatment protocol. Monthly, two-hour group supervision supports the EMDR therapist for the whole duration of the data collection phase. Between supervision sessions, the consultant is available for consultation by email. All EMDR treatment sessions will be videotaped. A random selection will be rated for treatment fidelity by several independent raters with EMDRIA approved basic training. Deviations from the protocol will be reported to the consultant and EMDR therapist.

Since participants are randomized and TAU is therefore assumed equal in both groups, no fidelity checks are done regarding TAU.

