### Analyses

All analyses will be executed using SPSS. Summary tables will be provided for all baseline, end of treatment and follow-up variables. Data will be summarised using frequency tables (with confidence intervals when applicable), and descriptive statistics (mean, median, interquartile range, number and percentages of participants and two-sided, 95% confidence intervals when appropriate).

Changes in the number of heavy drinking days in the past 30 days will be used to analyze the efficacy and effectiveness of EMDR. Since this primary outcome variable is continuous, a repeated measures ANOVA will be carried out with 2 group (EMDR + TAU versus TAU) and 4 time (pre-, post-treatment, 1 and 6 month follow-up) factors. Randomization stratum will be used as a covariate. Effect sizes will be calculated.

All allocated participants will be included in the primary analysis (intention-to-treat, ITT). Since an ideal ITT requires a complete set of data [89], multiple imputation (or a similar strategy) will be used for missing data, if possible. In addition a per-protocol (PP or completers) analysis will be done. ITT analyses will provide insight into the effectiveness of the treatment in real life whereas PP analysis gives insight into the efficacy or the ability for the treatment to reach its intended effect under ideal circumstances.

Repeated measures of continuous secondary variables such as time to first alcohol consumption, number of total drinks consumed and average drinks per occasion in the past 30 days, severity of the dependence, level of rumination, negative affect, desire thinking, craving, coping self-efficacy, quality of life, biomarkers will be analyzed by carrying out a repeated measures ANOVA with 2 group (EMDR + TAU versus TAU) and 3 (post treatment versus 1 versus 6 month follow-up: time to first drink variable derived from TLFB data) or 4 time (pre- versus post-treatment versus 1 versus 6 month follow-up: all other data) factors.

Distribution of premature treatment termination (PTT), a categorical variable, will be analysed using chi-square tests. A range of baseline clinical characteristics potentially associated with subsequent PTT will be examined. A logistic regression analysis will be conducted to examine the relative contribution of key variables to PTT status. A Kaplan–Meier survival curve will be used to illustrate the distribution of PTT prior to the completion threshold at session 5.

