Group equivalence will be analyzed using independent t-tests to compare the experimental with the control group on continuous baseline or pretreatment measures of severity and duration of alcohol dependence, motivation to change, coping self-efficacy, quality of life, craving, desire thinking, rumination, negative affect and biomarker levels of GGT and CDT. Group equivalence of categorical variables, such as level of education, history of other substance use, specific contents of TAU use of anti-craving, abstinence enforcing or other psychoactive medication during the study treatment phase and co morbidity will be analyzed using chi-square tests.

Variables such as use of anti-craving, abstinence enforcing or other psychoactive medication, time-in-treatment, craving, rumination, negative affect and desire thinking at T0, may be used as covariates after determining correlations with other primary and secondary outcome measures.

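### Variables measured after randomisation are listed as covariates; used in secondary or optional between-arm models, they can bias the EMDR effect in either direction

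*Protocol article*

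**What the plan says.** Five places in the protocol article bear on this.

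- **Secondary objectives.** The purpose is exploratory: "To explore mechanisms of change, variables that are potential predictors, mediators or moderators of treatment outcome will be examined". Under a *Covariates* label there are two lists. One holds baseline variables. The other reads "Measured between baseline and follow-up: completer status, time-in-treatment, treatment intensity, the use of psychopharmaca" and goes on to anticraving and abstinence-enforcing medication. Time-in-treatment is in both lists.
- **Treatment as usual (TAU).** "TAU may differ in intensity or additional components delivered (e.g. family treatment) between participants". Regular therapists decide how long TAU continues, and it can be supplemented with medication or in-patient care. Time-in-treatment "during the course of the study as well as main components and treatment intensity of TAU will be registered", and medication is monitored.
- **Fidelity checks.** "Since participants are randomized and TAU is therefore assumed equal in both groups, no fidelity checks are done regarding TAU".
- **Termination of treatment.** A completer has at least five of seven EMDR sessions in the EMDR arm. For TAU, a completer has at least five weeks with weekly contact between T0 and T1.
- **Analyses.** For the primary repeated measures ANOVA, "Randomization stratum will be used as a covariate"; no other covariate is fixed. In the group-equivalence paragraph, the contents of TAU and use of anti-craving, "abstinence enforcing or other psychoactive medication during the study treatment phase and co morbidity will be analyzed using chi-square tests", alongside baseline characteristics. The closing paragraph permits medication use, time-in-treatment, craving, rumination, negative affect and desire thinking as covariates, once their correlations with the outcome measures are known. The words *at T0* follow the last item only.

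**The concern.** Randomisation balances the patients at T0. It does not balance the care they receive afterwards. Regular therapists choose that care, and the Randomization and allocation section does not name them among those blinded to allocation. If EMDR changes drinking, attendance or a therapist's view of need, then TAU intensity, medication and completion may differ by arm because of the allocation.

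A model that holds such a variable constant no longer estimates the effect of adding EMDR to TAU. It removes any part of the effect that runs through the variable. It also compares patients who reached the same value for different reasons. Completer status is the plainest case, since the same code stands for different behaviour in each arm.

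Choosing covariates by their observed correlation with the outcomes makes this worse, because variables downstream of drinking are likely to correlate with it. At stake is the credibility of any adjusted secondary or supporting estimate of the EMDR effect, and a clear account of the co-treatment each arm received.

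**Working it through.** **1. The plan's own figure.** Power and sample size calculation gives changes of 8.7 (SD 12.5, n = 618) and 12.5 (SD 12.2, n = 362) heavy drinking days.

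- Pooled SD = √[(617 × 12.5² + 361 × 12.2²)/978] = 12.39.
- d = 3.8/12.39 = 0.307 and f = d/2 = 0.153, against the stated 0.31 and 0.15.
- With f = 0.15, 2 groups and 3 measurements, λ = f²·N·3/(1 − ρ), df = 2 and 2(N − 2). Assuming ρ = 0.5 and sphericity (neither is stated), N = 74 with power 0.806.

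The stated 74 reproduces, and nothing in this point alters it. The 3.8 days is itself a contrast between under- and overtreated patients, so treatment intensity is plausibly on the causal path.

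**2. Which model uses which covariate.**

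| Variable | Primary ANOVA | Secondary objectives, after baseline | Optional list in Analyses |
|---|---|---|---|
| Randomisation stratum | yes | no | no |
| Completer status | no | yes | not named |
| Treatment intensity | no | yes | not named |
| Time-in-treatment | no | yes | yes, *at T0* unclear |
| Medication | no | yes | yes, *at T0* unclear |

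**3. Adjusting for completer status (all inputs assumed).** One million simulated patients per row, outcome SD 12.39. A latent prognostic factor loads 0.7 on completion and correlates r with the outcome. Completion itself is worth 0 or 4 days. Entries are the adjusted effect in days; positive means a larger reduction with EMDR.

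| Completion EMDR / TAU | True effect | r = 0.3, worth 0 | r = 0.3, worth 4 | r = 0.5, worth 0 | r = 0.5, worth 4 |
|---|---|---|---|---|---|
| 67% / 67% | 0 | −0.02 | 0.01 | −0.02 | 0.01 |
| 60% / 75% | 0 | 0.63 | 1.24 | 1.10 | 1.69 |
| 75% / 60% | 0 | −0.62 | −1.27 | −1.07 | −1.64 |
| 60% / 75% | 3.8 | 4.43 | 4.99 | 4.88 | 5.50 |
| 75% / 60% | 3.8 | 3.19 | 2.56 | 2.74 | 2.13 |
| 50% / 80% | 0 | 1.29 | 2.50 | 2.14 | 3.39 |

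The unadjusted estimate stays within 0.06 of the truth in every row. There is no bias when completion is equal; when it is not, the sign follows which arm completes more.

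**4. Adjusting for a step-up in TAU (all inputs assumed).** With u a standard normal patient factor and g = 1 for EMDR:

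- early drinking = 10 + 6u − 3.8 × 0.78g + N(0, 5)
- logit of step-up = −1 + k(early − 8)
- late drinking = 10 + 6u − 3.8g − b × step-up + N(0, 5)

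Step-up occurs in 33% of TAU and 27% of EMDR patients for k = 0.1, and in 40% and 30% for k = 0.2. Reductions in days, which vary by a few hundredths between runs:

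| k | b (benefit of step-up) | Total effect | Adjusted effect |
|---|---|---|---|
| 0.1 | 0 | 3.81 | 3.63 |
| 0.1 | 3.8 | 3.59 | 3.63 |
| 0.2 | 0 | 3.80 | 3.33 |
| 0.2 | 3.8 | 3.45 | 3.33 |
| 0.2 | 5 | 3.33 | 3.33 |
| 0.2 | 6 | 3.24 | 3.33 |

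A clear loss appears only if stepped-up care does nothing. As it becomes effective, the loss shrinks, vanishes and then reverses.

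**The case against.** The defence is strong on several counts. The list of variables measured after baseline belongs to an exploratory objective on mechanisms, where studying treatment intensity or completion is legitimate. The primary model names stratum only. The optional covariates are permitted, not required, and *at T0* may govern the whole list. Adjustment sets for secondary models are commonly left to the analysis plan, which is not shown. In the step-up example, even the largest shift (3.80 − 3.33 = 0.47 days) is small beside a standard error of about 12.39 × √(2/37) = 2.9 days for a simple comparison of change in 74 patients.

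Most of this stands, and it rules out four stronger readings that a reader might infer:

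- *The primary analysis adjusts for care received after randomisation.* It does not, as the stratum sentence shows.
- *Medication and completion are assumed equal.* The assumption covers TAU only and is given as the reason for omitting fidelity checks. TAU contents and medication are compared by chi-square, and premature termination is analysed as an outcome.
- *Differences in co-treatment would be hidden.* TAU components and intensity are registered, and part of this is already tested by arm.
- *Adjustment dilutes the EMDR effect by a known fraction.* Neither the direction nor the size is fixed. The text also does not say that therapists set TAU by drinking; that is a plausible inference.

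Two things survive. The article does not merely leave the adjustment set open: it labels variables measured after T0 as covariates and states an outcome-driven selection rule that reaches the primary outcome. And the step from randomisation to equal delivered TAU is wrong as reasoning, whatever an analysis plan adds.

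**Conclusion.** The point holds as an avoidable risk in secondary or optional adjusted between-arm analyses. Completer status, treatment intensity, time-in-treatment and medication after T0 can be affected by allocation, and completer status is not the same variable in both arms. Adjusting for any of them can bias the EMDR effect up or down if it differs by arm, and does nothing of the kind if it does not.

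The document gives no completion rates, TAU doses or medication rates by arm, so the size is unknown. The simulated figures rest wholly on assumed inputs: shifts of 0.6 to 1.7 days either way for completion of 60% against 75%, up to 3.4 days for 50% against 80%, and at most about 0.5 days in the step-up example. They show that the direction is open; they are not forecasts.

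Separately, equality of TAU after T0 does not follow from randomisation and sits badly with the article's own statement that TAU may vary. The planned sample size and the primary ANOVA as written are unaffected.

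**What to change.** - **Analyses:** state that every model estimating a between-arm effect adjusts only for randomisation stratum and pre-specified values recorded at or before T0. Reword the closing paragraph so that *at T0* governs the whole list, and drop selection by observed correlation with the outcomes.
- **Secondary objectives:** take the variables measured after T0 out of the covariate label and keep them for exploratory mediation analyses labelled as such.
- **Fidelity checks:** remove the statement that TAU is assumed equal because participants are randomised.
- **Reporting:** move TAU contents and medication during the study out of group equivalence. Report TAU intensity, components and medication after T0 by arm, for T0 to T1 and T1 to T3, as co-treatment delivered.

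The cost is a few sentences and one table from data already being registered. There is no new data collection and no change to the sample size.
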